**Methods:**

The study is a multicentric randomized controlled trial, which will be conducted across 4 phases in Udupi, Mysuru, and Shivamogga districts of Karnataka. Phase 1 features a cross-sectional study design of 175 farmers to evaluate their baseline knowledge, attitudes, and practices on usage of pesticides. Phase 2 employs semi-structured interviews with 20–30 farmers and 10–20 key stakeholders, including pesticide dealers, scientists from Farm Science Centers [Krishi Vigyan Kendra (KVK)], and joint directors of agriculture to explore pesticide handling approaches, challenges, and community-specific needs while handling pesticides. The findings from Phases 1 and 2 will help in development and validation of an intervention in the form of educational video in Phase 3 which will be piloted. Phase 4 involves implementing the validated intervention and conducting long-term follow-up to assess the impact and sustainability. Phase 4 will be a two-arm, single-blind, parallel-group randomized controlled trial, with villages randomized 1:1 into intervention and control groups. The intervention group will receive a 15–20-minute educational documentary in the local language, while the control group will receive no intervention. The outcomes will be evaluated based on changes in Knowledge, Attitudes, and Practices (KAP) scores, with assessments conducted immediately post intervention, at 6 months, and at 12 months from the date of intervention. These will be correlated with outcomes including quality of life and laboratory parameters.

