### Trial design

This study adopts a multi-phase, mixed-methods approach to address pesticide safety practices among farmers in Karnataka state. The study will be conducted in 4 different phases. Phase 1 is an analytical cross-sectional study, designed to evaluate the baseline knowledge, attitudes, and practices (KAP) of farmers using structured questionnaires. Phase 2 involves qualitative face-to-face interviews to gain deeper insights into the behavioural and contextual factors influencing pesticide usage and safety practices.

Phase 3 involves development and validation of need-based education module, where selection of experts will be carried out by purposive sampling technique. Phase 4 is a multicentric RCT, where 3 districts that includes 6 villages will be selected based on randomization. This study will be conducted as a two-arm, single-blind, parallel group with simple randomization of the districts and cluster randomization of farmers. The allocation ratio is 1:1, with one arm receiving the educational intervention and the other serving as a control group with no intervention. The outcomes will be assessed in terms of mean difference with the pre and post assessment in terms of KAP. The trial adopts a superiority framework [33] to assess the effectiveness of the educational intervention in improving pesticide safety knowledge, attitudes, and practices among farmers.

The below Fig. 1 depicts the trial process from recruitment to randomisation.

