In phase 4, the same villages from Phase 1 will be selected for recruitment. The districts will be randomized into control and intervention groups. Farmers will be identified using cluster sampling, with stratification based on age and agricultural experience. The intervention will be delivered to the experimental group at village halls or community centres. The cluster sampling approach ensures that participants are diverse in terms of age, educational level, and years of experience in agriculture allowing for a balanced representation across the groups.

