## Methods: assignment of interventions (for controlled trials)

### Random sequence generation and randomization

The allocation sequence will be generated using a computer-generated random number table through simple randomization. Participants who enroll in the study will be assigned with a unique identification code in alphabetical order. In Phase 4, villages will first be randomized into intervention or control groups. Within each group, participants will be categorized using a cluster randomization technique, accounting for confounding factors such as age, gender, education level, and agricultural experience. Stratification will further ensure balance by considering key variables like crop varieties and pesticide spraying techniques.

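### The article assigns districts to arms in one place and villages in others; three districts cannot be split 1:1, and simple randomisation of six villages assures neither the 1:1 ratio nor balance across districts

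*Protocol article*

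**What the plan says.** The article describes Phase 4 allocation in four places.

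- **Recruitment of participants:** "The districts will be randomized into control and intervention groups". The same paragraph says that Phase 4 reuses the Phase 1 villages.
- **Trial design:** "3 districts that includes 6 villages will be selected based on randomization", followed by "simple randomization of the districts and cluster randomization of farmers". It also states "The allocation ratio is 1:1".
- **Abstract, Methods:** "with villages randomized 1:1 into intervention and control groups".
- **Random sequence generation and randomization:** "The allocation sequence will be generated using a computer-generated random number table through simple randomization", then "In Phase 4, villages will first be randomized into intervention or control groups". Later in the same paragraph: "Stratification will further ensure balance by considering key variables like crop varieties and pesticide spraying techniques".

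The districts are Udupi, Mysuru and Shivamogga. The number of villages per district is not given, and district is not named as a stratification factor for allocation.

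**The concern.** The unit of randomisation decides what trial is run. Two teams working from this text could implement different designs: one allocating three districts, the other six villages. The first cannot meet its own allocation ratio, and at least one arm would consist of a single district or of none. The second can meet the ratio, but simple randomisation does not guarantee it and does nothing to spread the arms across districts.

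District matters here. Study setting names crop mix and local farming practice among the grounds for choosing sites, so the article itself treats regional differences as relevant. If arm and district coincide, a difference between arms may be a difference between districts. That cannot be undone after allocation.

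**Working it through.** **Inputs.** Three districts, six villages and a 1:1 ratio (Trial design); simple randomisation (randomisation section). Assumption: two villages per district, because the article does not give the split; alternatives are shown. The 1:1 ratio is a design target, so there is no calculated figure of the plan's to reproduce. The check is whether each reading can deliver it. Simple randomisation is taken first as independent draws with probability 1/2.

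**Reading A: the district is the unit.**
- Three is odd, so an equal split does not exist.
- There are 2³ = 8 assignments. All three districts fall in one arm in 2/8 = 25%; the split is 2:1 or 1:2 in 6/8 = 75%.
- In every 2:1 split, one arm is one district.

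**Reading B: the village is the unit, independent draws.** There are 2⁶ = 64 assignments.

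| Split | Count | Probability |
|---|---|---|
| 3:3 | 20 | 31.25% |
| 4:2 | 30 | 46.9% |
| 5:1 | 12 | 18.75% |
| 6:0 | 2 | 3.1% |

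An unequal split therefore occurs in 44/64 = 68.75%.

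With two villages per district:
- Both arms appear in a given district with probability 1/2, so in all three with probability (1/2)³ = 12.5%.
- At least one district lies wholly in one arm in 1 − 0.125 = 87.5%.
- Every district lies wholly in one arm in (1/2)³ = 12.5%.

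**Reading C: the village is the unit, 3:3 forced but not stratified by district.** There are C(6,3) = 20 assignments.
- Both arms appear in every district in 2³ = 8 of them, or 40%.
- At least one district lies wholly in one arm in 12/20 = 60%.
- Complete confounding is impossible with two villages per district, since three villages cannot be made up of whole pairs.

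**Sensitivity to the assumption.**
- With villages split 1/2/3 or 1/1/4 across districts, at least one district is always in one arm only, because a district with one village can hold only one arm.
- If six villages meant six per district (18 in all), an exact 9:9 split under independent draws would have probability C(18,9)/2¹⁸ = 18.5%, but confounding with district would be much weaker.

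**Comparison: allocation within district, one village per arm in each.** There are 2³ = 8 assignments; all are 3:3 and all have both arms in every district. The smallest attainable two-sided randomisation p-value is 2/8 = 0.25, against 2/20 = 0.10 for an unrestricted 3:3.

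**The case against.** **Only one sentence plainly assigns districts to arms.** Trial design speaks of selecting sites by randomisation, so its phrase about districts could mean selection. A reader might count two statements for districts against two for villages; the text does not firmly support that count. The selection reading is itself uneasy, since Study setting and the recruitment section choose the districts on purpose. The conflict between the recruitment section and the randomisation section stands in any case.

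**A stated 1:1 ratio may imply three of six villages drawn from the random number table.** This is a fair reading, and on it 3:3 is certain. A reader might infer that 1:1 will usually fail with villages; that follows only if simple means independent draws. The 60% figure then replaces the 87.5%.

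**Village allocation is not fully confounded with district.** This is correct. With two villages per district, complete confounding occurs in 12.5% of independent draws and never under a forced 3:3. In the other allocations that leave some district in a single arm, the confounding is partial.

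**Stratification might help.** The sentence on crop and spraying technique is separate from the one about balancing participants within each group, and could apply to villages before allocation. So one cannot say that all the balancing happens after allocation. But it does not name district, and it sits beside an instruction to use simple randomisation.

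**Outcomes are changes from baseline.** Stable differences in level between districts therefore largely drop out. Differential change over the follow-up year does not.

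**The 1:1 ratio might refer to farmers.** Nothing says so: Phase 1 recruits equal numbers per district and Phase 4 returns to those villages. Even so, one arm would still be a single district.

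**Conclusion.** The point holds. The article gives two units of randomisation and no rule for choosing between them. This is a contradiction in what is stated, not detail left to a fuller document.

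Under district allocation, the failure of 1:1 and the confounding of arm with district are certain and rest on no assumption; the 25% chance that one arm is empty assumes independent draws. Under village allocation the problem is one of risk. The 31% chance of an exact 3:3 depends on independent draws. The 60% chance (forced 3:3) or 87.5% chance (independent draws) that some district falls in a single arm depends on two villages per district. The documents do not support saying that village allocation is wholly confounded with district, or that its ratio must fail.

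This should be settled before allocation, because it determines whether the comparison between arms can be interpreted.

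**What to change.** 1. Name the village as the unit of randomisation throughout, and describe the design as cluster randomisation of villages.
2. Remove the statements in Trial design and Recruitment of participants that districts are randomised to arms.
3. Replace simple randomisation with 1:1 allocation of villages within each district. State the number of villages per district and a rule for an odd number.
4. Account for district in the analysis.

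**Cost.** Protocol wording and a short allocation list stratified by district.

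**Downsides.** Both arms would be present in each district, so spill-over between villages must be considered. Study setting already favours interior villages, but it says nothing about distance between them, and Phase 4 is tied to the Phase 1 villages. With one village per arm per district there are only eight possible allocations, so a two-sided randomisation test cannot go below p = 0.25. Stratifying removes an avoidable source of confounding; it does not cure the small number of clusters.

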## Methods: assignment of interventions (for controlled trials)

### Random sequence generation and randomization

The allocation sequence will be generated using a computer-generated random number table through simple randomization. Participants who enroll in the study will be assigned with a unique identification code in alphabetical order. In Phase 4, villages will first be randomized into intervention or control groups. Within each group, participants will be categorized using a cluster randomization technique, accounting for confounding factors such as age, gender, education level, and agricultural experience. Stratification will further ensure balance by considering key variables like crop varieties and pesticide spraying techniques.

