### Intervention

The primary component of the intervention will be a 15–20-minutes educational documentary in the local language. Topics like safe pesticide usage, proper storage, disposal methods, and associated health risks will be covered in this documentary. These elements will be presented through a story that will be displayed as a short documentary or movie among the farmers. Cluster sampling method will be utilised for selecting participants based on characteristics including age, education, and years of experience with pesticides or agriculture. The intervention will be provided in the intended villages at community centres or village halls.

The control group will not receive any educational intervention during the study period. Participation records will be maintained to track adherence to intervention, and any participant’s decision to withdraw from the study will be documented. If withdrawn, data collected up to the point of withdrawal will be retained for analysis. The appropriate reason will be documented for withdrawal if available.

To maintain the integrity of the study, participants will be requested to refrain from engaging in other pesticide-related educational initiatives, although they may continue their regular farming activities. Adherence to the intervention and pesticide practices will be monitored through regular follow-up calls, personal visits, and collaboration with field officers, community leaders, and local organizations.

The detailed participant timeline has been provided in Fig. 2, following the SPIRIT 2025 format [39] .

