For Phase 4, the sample size was determined based on findings from a pilot study involving 12 farmers, with equal allocation to intervention and control groups in a simple randomized controlled trial (RCT) design. The final sample size was calculated using the power calculation formula for a paired t-test:$$\mathrm{n}\;=\;2\times\;[(\mathrm{Z}_{\alpha/2}\;+\;\mathrm{Z}_{\beta})^{2}\;*\;2\sigma^{2}\;/\;\mathrm{Z}_{\delta}\:^{2}]$$, where, n = required sample size per group, Z_α/2_**=** standard normal deviate for a given significance level (e.g., 1.96 for 5% significance level), Z_β_ = standard normal deviate for the desired power (e.g., 0.84 for 80% power), σ = standard deviation of the outcome variable (10.33 from prior study) and Z_δ_ = expected mean difference in the effect size.

To ensure the effective implementation of the educational intervention, farmers will be stratified by age and education level.

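### Stratification is said to ensure balance between arms, but the village allocation is unrestricted, farmers are categorised only afterwards within each arm, and the named stratifiers disagree

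*Protocol article*

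**What the plan says.** All references are to the protocol article.

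- **Order of steps** (Random sequence generation and randomization). The sequence is computer-generated by simple randomization. Then: "In Phase 4, villages will first be randomized into intervention or control groups". Farmers come next: "Within each group, participants will be categorized using a cluster randomization technique, accounting for confounding factors such as age, gender, education level, and agricultural experience".
- **Assurance** (same section). "Stratification will further ensure balance by considering key variables like crop varieties and pesticide spraying techniques". The Phase 4 text under Recruitment of participants adds that cluster sampling makes the groups comparably represented on age, education and experience.
- **Stratifiers elsewhere.** Sample size, Phase 4: "farmers will be stratified by age and education level", with effective delivery of the intervention given as the purpose. Recruitment of participants, Phase 4: "Farmers will be identified using cluster sampling, with stratification based on age and agricultural experience". Intervention: cluster sampling is used for "selecting participants based on characteristics including age, education, and years of experience with pesticides or agriculture".
- **Clusters** (Trial design). Three districts with 6 villages, allocated 1:1.

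The article does not stratify, block, match or otherwise constrain the allocation of villages. It sets no stratum levels and no quotas common to both arms.

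**The concern.** In a cluster design, a farmer's arm is settled when the village is allocated. Stratification protects the comparison between arms if it restricts that allocation, or if farmers are then sampled to the same composition in both arms. The article describes neither, yet presents balance as secured.

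Two things are at stake. First, with so few villages, chance imbalance on anything that differs between villages is likely, and a reader relying on the assurance would not expect it. A difference between arms in education, experience or cropping could then be read as an effect of the documentary on the KAP scores. Second, farmers are to be chosen by characteristics after the arms are set, by criteria that vary between sections. The Blinding section says study personnel other than participants are not blinded. That leaves room for differently composed samples in the two arms.

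**Working it through.** The article gives no figure for balance, so there is none to reproduce. The check compares the sections and then counts the possible allocations.

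**Inputs.** 6 villages in 3 districts and a 1:1 ratio (Trial design); simple randomization of villages before farmers are categorised (Random sequence generation and randomization). I take simple randomization to mean that each village is allocated independently with probability 1/2. Results for a forced 3:3 split are also given, in case that is what is meant.

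**Step 1: stratifiers side by side.**

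| Section | Factors | Role stated |
|---|---|---|
| Sample size (Phase 4) | age, education | stratify farmers, for delivery |
| Recruitment (Phase 4) | age, agricultural experience | stratify when identifying farmers |
| Intervention | age, education, years of experience (open list) | select farmers |
| Random sequence generation | age, gender, education, experience (open list); also crop and spraying technique (open list) | categorise within group; ensure balance |

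The first two rows are closed lists for the same Phase 4 farmers, and they differ. The last row adds further factors.

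**Step 2: does the allocation reach 1:1?**

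- Possible allocations: 2^6 = 64.
- 3:3 split: C(6,3)/64 = 20/64 = 31.3%.
- 5:1 or 6:0 in either direction: 2 × (6 + 1)/64 = 14/64 = 21.9%.
- All villages in one arm: 2/64 = 3.1%.

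**Step 3: a trait shared by whole villages** (assumed, for example the dominant crop).

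- Present in 2 of 6 villages, simple randomization: both in the same arm in 2 × 2^4 = 32 of 64 allocations, 50%.
- Present in 2 of 6, forced 3:3: 2 × C(4,1) = 8 of C(6,3) = 20, 40%.
- Present in 3 of 6, forced 3:3: wholly in one arm in 2/20 (10%) and divided 2:1 in 18/20 (90%). An even division is impossible.

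Categorising farmers within arms afterwards changes none of these probabilities.

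**Step 4: what restriction would gain.** Assume two villages per district, which the article does not state. Every district then has one village in each arm with these probabilities:

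- simple randomization: 2^3/64 = 8/64 = 12.5%;
- forced 3:3 without strata: 8/20 = 40%;
- allocation stratified by district: 8/8 = 100%.

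**The case against.** **Sampling can align arms.** A reader might infer that stratification after allocation balances nothing. The documents do not support that. The Recruitment section applies stratification when farmers are identified, which is a sampling step, and identical quotas in both arms would align the sampled farmers on the quota factors. This stands. What remains is that no common quotas are stated, and that quotas cannot supply a village-level trait that one arm's villages lack. An article may leave quota tables to the full protocol, but it should not then claim balance from the steps it does describe.

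**The factor lists overlap.** A reader might also infer that every section names an incompatible set. That goes too far. The lists under Intervention and Random sequence generation are open, the second contains the factors of the first, and the Recruitment section mentions education as well when it describes diversity. The Sample size sentence serves delivery, not balance. The firm discrepancy is between the two closed lists, with extra factors added in the randomization section.

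**The balance sentence may concern villages.** The phrase placing categorisation within each group belongs to the preceding sentence, so stratification by crop and spraying technique could refer to villages. On that reading it conflicts with the simple randomization stated in the same section, and the text still needs correction.

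**Shared traits and empty strata.** That crop and spraying technique are shared within villages is nowhere stated; it is an assumption here. Crossing six two-level factors would give 2^6 = 64 cells, and one might infer that most would be empty. The article does not say that the factors will be crossed or dichotomised and states no Phase 4 total, so I make no such claim.

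**Change scores.** Outcomes are analysed as changes from baseline, which removes stable differences in level. It does not remove differences in trend related to education, experience or crop.

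**Conclusion.** The concern holds in a limited form. As written, the design does not ensure balance between arms: the village allocation is unrestricted, farmer categorisation follows it within each group, and no common quotas are given. Stratification could still help on farmer-level factors if the same quotas were applied in both arms.

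Under simple randomization of 6 villages, the intended 3:3 split arises in 31% of allocations. A trait confined to two villages falls wholly in one arm in 50%, or 40% with a forced 3:3 split. These figures assume independent allocation with probability 1/2 (or exactly 3:3), and a trait that is uniform within villages. They also take the village as the unit. The Recruitment section randomises districts instead; that is a separate conflict, and three districts cannot divide 1:1.

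The stratifiers for Phase 4 farmers contradict each other between Sample size and Recruitment, whatever view is taken of the open lists. This does not invalidate the trial, but it should be corrected before Phase 4 allocation.

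**What to change.** 1. Reconcile Sample size, Recruitment of participants and Random sequence generation to one short farmer-level factor set, for example age band and education, and align the Intervention section with it.
2. Draw up the farmer list before allocation and apply the same quotas in every village. Phase 4 returns to the Phase 1 villages, so the list can be prepared there.
3. Settle whether the unit is the village or the district, then replace simple randomization of villages with restricted allocation. If the sponsor confirms two villages per district, stratify by district. Otherwise constrain the allocation to 3:3 using each village's crop and spraying profile.
4. Adjust the comparison between arms for the chosen baseline factors.
5. Delete the statement that stratification ensures balance, or limit it to the factors on which allocation or quotas actually act.

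**Cost.** Protocol wording, and a village and farmer list prepared before allocation. No extra farmers are needed. Fewer factors are formally stratified, and stratifying by district leaves 2^3 = 8 possible allocations instead of the 20 under an unstratified 3:3 split.
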